#### Seizure status

Tumor-associated seizures are defined as any unprovoked seizure occurrence with evidence of a concordant tumorous lesion in MRI examinations prior to surgery. During the baseline visit, seizure frequency will be assessed as the average number of seizures per month. Seizures will be classified based on their origin in the brain, the degree of awareness during the seizure, and the level of body movement, following the 2017 classification of the ILAE commission on classification and terminology [32]. Focal onset seizures will be categorized as focal aware (including the former term aura), focal impaired awareness, focal motor onset, focal non-motor onset, or focal to bilateral tonic–clonic. Generalized onset seizures will be categorized as generalized motor (tonic–clonic) or generalized non-motor (absence).

Postoperative seizure outcome will be analyzed based on seizure status at 12 weeks, 6 months, and each subsequent 12-week follow-up examination. Seizure outcomes will be classified according to the ILAE system used for epilepsy surgical procedures. Favorable seizure outcomes will be defined as seizure freedom (ILAE class 1), while unfavorable outcomes will include ILAE classes 2–6, covering pure auras, rare to no improvement, or worsening of seizure frequency [50]. Detailed information on the ILAE classification system for postoperative seizure outcome is presented in Fig. 5.

**Fig. 5 Fig5:**
[figure not shown]
Graphical overview of the ILAE classification system for assessing postoperative seizure outcome. Scheme adapted from Wieser et al. [68]. ILAE, International League Against Epilepsy; yr, year

In addition to documenting seizure status according to the ILAE classification, electroencephalography (EEG) will be performed preoperatively during the baseline visit (Visit 2) and postoperatively at 30 days after surgery (Visit 7). EEG reports must note any pathological findings and specify whether these include epileptiform activity, status epilepticus, focal findings, or other abnormalities. Additional EEG recordings may be performed at any time but are not mandatory.

#### Perioperative complications

Postoperative complications will be assessed by PSIs [33] and specific CSCs as previously described [34].

PSIs introduced by the Agency of Healthcare and Quality [33] will entail pressure ulcer, iatrogenic pneumothorax, vascular catheter-related infection, transfusion reaction, retained surgical item, peri- and postoperative hemorrhage, acute postoperative respiratory failure, pulmonary embolism, deep venous thrombosis, postoperative sepsis, wound dehiscence, accidental puncture or laceration, postoperative hip fracture, postoperative physiologic and/or metabolic dearrangement. Peri- and postoperative hemorrhage will be defined as PSI in case they will require further surgical therapy.

CSCs will consist of postoperative ischemic infarction, cerebro-spinal fluid leakage, wound infection, atrophic wound healing disorder, postoperative meningitis and/or ventriculitis, emypema and postoperative permanent new or worsened neurological deficits including speech and language deficits [34]. Postoperative cerebrospinal fluid leakage will be defined as CSC if further surgical/interventional therapy (surgical wound examination, transient insertion of a lumbar drainage system and/or surgical insertion of a permanent shunt system) is required. Wound infection and postoperative meningitis will be defined as CSC, if further antibiotic-based and/or surgical therapy is needed.

PSIs and CSCs will be divided into early postoperative complications occurring within the time span of day 0 until day 30 (Visit 7) as previously described [34] and late postoperative events occurring from day 31 until day 90 (Visit 8).

The outcome will be documented as resolved, resolved with sequelae, ongoing at end of study or death.

Furthermore, iatrogenic damage of the middle cerebral artery (MCA) and/or its lenticulostriate branches, the anterior choroidal artery, and the P2 segment of the posterior cerebral artery (PCA) will be collected as intraoperative complications specifically related to temporomesial surgery.

#### Surgery-related data

Details of the surgical procedure will include the duration of the surgery, measured from incision to the completion of suturing, as well as the method of dural closure and whether a subgaleal drain was inserted. Intraoperative seizures, if any, must be documented, including their semiology, frequency, and the medications administered to manage them. Additionally, the amount of blood loss, the number of units of red cell concentrates and platelets transfused, and any clotting factors substituted must be recorded.

The use of adjunct technologies during surgery is optional and left to the discretion of the treating neurosurgeon. These include the administration of 5-ALA or other fluorescent dyes, the use of intraoperative MRI, and the performance of awake surgery.

Intraoperative neuromonitoring (IOM) will include the intraoperative recording of somatosensory evoked potentials (SEPs) and motor evoked potentials (MEPs). SEPs will be recorded following stimulation of the median nerve, with significant warning criteria defined as latency increases of > 10% or amplitude decreases of > 50%, whether transient or permanent [69, 70]. These changes must be documented in the eCRF.

For MEP measurements, subdermal needle placements will include the musculus abductor pollicis brevis (thenar), musculus adductor digiti minimi (hypothenar), and musculus tibialis anterior (lower extremity). A decline in MEP amplitude of > 50%, not attributable to technical issues, will be regarded as significant deterioration and must also be documented in the eCRF.

#### Orthoptic examination

An orthoptic examination, including the assessment of visual acuity and visual fields, will be conducted preoperatively during the baseline visit (Visit 2) and postoperatively 14 days after surgery (Visit 6). Any pathological findings must be documented in the examination report and specified in detail if observed.

#### Histopathological and molecular genetic results

The fresh frozen section procedure, mandatory for randomization, requires at least three of the four criteria defined by the WHO grading system to be met in support of the diagnosis of a diffuse high-grade glioma [71]. These criteria include high cellularity and mitotic activity, a diffuse infiltration pattern, microvascular proliferation, and necrosis.

Final histopathological findings confirming glioblastoma (CNS WHO grade 4), IDH wildtype, must be recorded in the eCRF. If other histological findings are identified that were classified as a diffuse high-grade glioma in the fresh frozen section procedure, they must be specified in the eCRF. Additionally, the MGMT promoter methylation status should be determined and categorized as hypermethylated (hypermethylation of the MGMT promoter), nonmethylated (no hypermethylation of the MGMT promoter), or not available/inconclusive. Optionally, any additional results from histopathological or molecular pathology analyses can also be entered into the eCRF.

#### MRI protocols

All MRI examinations have to include the following sequences:Pre-contrast injection: T2-w (e.g., turbo-spin-echo, TSE); T2-FLAIR; 3D T1-w (e.g., gradient-echo, GRE; or T1-w in two planes, one of them axial)Post-contrast injection: 3D T1-w (e.g., gradient-echo GRE; or T1-w in two planes, one of them axial)

Additional sequences are optional but can be included at the discretion of the treating physician.

For T2, FLAIR, DWI, and SWI/T2* sequences that are not performed in 3D, it is recommended to acquire the images in the axial plane to ensure structured and comparable evaluation. To ensure the reproducibility of MRI evaluation, all MRIs have to be reviewed post-hoc by the reference neuroradiologist [name]. [name] (Department of Neuroradiology, University Hospital Bonn). The MRIs will be sent blinded regarding the participating center (only labelled with the Randomization-ID) to the reference neuroradiologist to ensure an unbiased progression assessment.

Mandatory MRI examinations will be conducted as part of the standard treatment protocol. These include a preoperative MRI (baseline visit; any MRI performed within one week prior to surgery can be considered as the baseline MRI), an early postoperative MRI (performed within 72 h after surgery), and follow-up MRIs every three months after surgery. Additionally, a post-radiation MRI within four weeks of completing radiotherapy is recommended but not mandatory.

To evaluate protocol adherence regarding the surgical procedures in the experimental (ATL) and control (GTR) arms, the 72-h postoperative MRI will be reviewed by two experienced neurosurgeons. The resection results will be graded as follows:GTR: Resection cavity without remaining contrast-enhancing tissue, subtotal resection, or partial resection.ATL: Anatomical boundaries for ATL (as described above) fulfilled or not fulfilled.

#### Concomitant and postoperative treatment/medication

All tumor-directed therapies, including RT, chemotherapy, TTFs, and immunotherapy, must be documented from day 1 prior to surgery (baseline visit) until the end-of-study visit. Additionally, all CNS-active medications, such as psychotropic drugs, seizure-suppressing medications, and anti-edematous treatments (necessary for RANO 2.0 classification [27]), must be recorded in the eCRF for the same period. Anticoagulant and antibiotic therapies should be documented from day 1 prior to surgery until at least the day 90 visit. While the recording of other long-term medications, such as blood pressure medication, gastric protection, or dietary supplements, is desirable for the entire study duration, it is not mandatory.

#### Adverse events

All AEs must be documented in the eCRF using the respective Adverse Event Report Form. Systematic collection and documentation of AEs will be conducted from the time of randomization until Visit 7 (Day 30 postoperative).

PSIs [33] and CSCs [34] are not classified as AEs in this trial and will be documented separately in the eCRF.

#### Data safety monitoring board (DSMB)

The DSMB is an independent committee tasked with monitoring the progress of the study, ensuring the safety of trial participants, and assessing the quality of the collected data through monitoring reports. It is responsible for providing recommendations regarding the continuation, modification, or discontinuation of the trial. The DSMB will convene once per year during the recruitment phase to review data on AEs, PSIs, and CSCs. Additionally, six months after the randomization of the 57th patient, the DSMB will review the results of the interim safety analysis. Based on this review, the DSMB may propose modifications to the trial, such as stopping the trial or amending the protocol.

The DSMB will consist of at least three members with expertise in neurosurgery, neurology, and biometrics, as well as experience in the conduct of clinical trials. It is charged with reviewing safety data from both arms of the trial and is empowered to stop the trial if evidence of harm is observed, but it does not have the authority to terminate the trial based on a lack of efficacy. Furthermore, the DSMB will provide insights on emerging therapeutic or diagnostic advances during the course of the trial that could influence the outcomes. If protocol modifications are deemed necessary, close collaboration between the DSMB, the SZB staff, and the study leadership will be required.

## Statistics and analysis

### Sample size calculation

The sample size calculation is based on the primary endpoints of OS and QoL, with equal allocation of subjects to the two treatment groups. Assuming a two-sided alpha level of 5%, median OS times of 17 months in the control group and 27.5 months in the experimental group, a 3-year accrual period, and a 3-year follow-up period (resulting in a total trial duration of 72 months), a total of 170 subjects with a confirmed diagnosis of glioblastoma will provide 80% power to test the null hypothesis of equal OS between the two groups (two-sided log-rank test). The assumed survival benefit of a 10-month improvement with ATL over GTR is based on existing data from retrospective glioblastoma surgery studies involving ATL [16, 25] as well as analyses of EORTC datasets that are not specific to temporal tumor localization [9].

It is anticipated that approximately 4.5% of randomized patients will not have glioblastoma CNS WHO grade 4 but rather a different subtype of diffuse high-grade glioma, as determined by the final integrated histopathological and molecular diagnosis according to the 2021 WHO classification [55]. If the final diagnosis does not confirm glioblastoma IDH wildtype (CNS WHO grade 4), these patients will remain in the trial for safety follow-up but will be replaced in their respective groups and excluded from the mITT population. This replacement strategy will result in a maximum of 178 randomized patients. All randomized patients, regardless of diagnosis, will undergo regular follow-up as outlined in the trial protocol for safety monitoring.

The two primary endpoints will be analyzed in a hierarchical order, with QoL being tested for non-inferiority in the experimental group compared to the control group if the null hypothesis for OS is rejected. QoL measurements will be conducted quarterly, and a prior study demonstrated an approximately linear time dependence of the QoL (= global health) score on time [49].

A simulation was performed to assess the non-inferiority of the slope of QoL scores over time in the two treatment groups, with a non-inferiority margin of 0.4 score points (using the quarter as the time unit). The simulation incorporated survival status based on the previously stated assumptions and assumed a compound symmetry for the correlation structure of QoL scores across time points, with a correlation coefficient of 0.7. The results indicate that a total of 170 evaluable subjects in the mITT population will provide approximately 80% power to test for non-inferiority of QoL (linear mixed-effects model with QoL score as dependent variable, random patient intercept, and treatment group + time as independent variables, 95% confidence interval of the interaction between time and treatment, 1000 Monte Carlo replications, mean power 83%, Monte Carlo error 1.2%).

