### Randomization

A unique feature of the ATLAS/NOA-29 trial is the intraoperative randomization process. Patients with imaging evidence suggestive of newly-diagnosed glioblastoma confined to the anterior temporal lobe will undergo craniotomy, typically performed as a pterional or temporal craniotomy, to allow for both temporal GTR and ATL. Once the dura is opened and tumor access is achieved, tumor tissue will be sent for frozen section analysis by the neuropathologist or pathologist in charge. Randomization will only occur after the (neuro)-pathologist has confirmed the diagnosis of diffuse high-grade glioma based on the frozen section results. The frozen section procedure, as performed in this study, is expected to prolong the surgery by approximately 10 to 20 min.

Randomization will be performed using the method of permuted blocks with variable block sizes. The randomization number will be assigned through the electronic case report form (eCRF) system, in a 1:1 ratio between the experimental (ATL) and control (GTR) interventions. Stratification will occur based on two criteria: age group (< 50 years or ≥ 50 years) and pre-operative KPS (70–80% vs. 90–100%).

Blinding of the surgical procedure is not feasible due to its inherent nature. The operating neurosurgeon and other treating physicians must review MRI scans during follow-up examinations, which will reveal the surgical approach. Consequently, the randomization process must be open.

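### Replacing non-glioblastoma patients within their own arm contradicts the stratified block randomisation, and 178 is an expected number rather than a maximum

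*Protocol article*

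**What the plan says.** Three places in the protocol article bear on this.

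- **Sample size calculation.** The target is set by the statement that "a total of 170 subjects with a confirmed diagnosis of glioblastoma will provide 80% power". Misclassification at frozen section is then allowed for: "It is anticipated that approximately 4.5% of randomized patients will not have glioblastoma CNS WHO grade 4". If the final diagnosis is not confirmed, "these patients will remain in the trial for safety follow-up but will be replaced in their respective groups and excluded from the mITT population", and "This replacement strategy will result in a maximum of 178 randomized patients".
- **Number of subjects.** All 178 are to be randomised 1:1.
- **Randomization.** "Randomization will be performed using the method of permuted blocks with variable block sizes", stratified by age group and pre-operative KPS, with the number issued through the eCRF during surgery. Because the surgery cannot be blinded, "Consequently, the randomization process must be open".

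The section on drop-outs and missing data adds that replaced patients are left out of the efficacy analysis. No section says how a within-arm replacement is issued by the eCRF, in which stratum or centre it is used, or whether a site is told about it.

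**The concern.** A replacement tied to the arm of the departing patient is not the next entry of a permuted-block list. The two instructions cannot both be followed as written. If the sample-size sentence is followed, some patients in the mITT analysis of OS and QoL have an arm fixed by an earlier patient's diagnosis.

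Concealment is also at stake. The trial is open, and Table 1 schedules the histopathology result at day 30, so the treating team knows the arm and learns that the diagnosis was not confirmed. Entry depends partly on the treating neurosurgeon's judgement: whether complete resection is achievable, whether other lesions belong to the tumour, and whether GTR would come close to ATL. If a team also knew that a place in one arm was owed, selection into that place would be possible, and variable block sizes would not prevent it.

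The second issue is the number itself. A replacement can also turn out not to be glioblastoma, so a fixed ceiling of 178 and a guaranteed 170 confirmed patients are not compatible.

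**Working it through.** **Inputs** (Sample size calculation): "Assuming a two-sided alpha level of 5%, median OS times of 17 months in the control group and 27.5 months in the experimental group"; 36 months accrual plus 36 months follow-up; 170 confirmed patients; 4.5% not glioblastoma; 178 randomised. Assumptions added here: exponential survival, uniform accrual, no loss to follow-up, and an independent 4.5% chance per patient.

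**1. The plan's own figures reproduce.**
- HR = 17/27.5 = 0.618, ln HR = −0.481.
- Probability of death by month 72 with hazard λ = ln 2/median: 1 − (e^(−36λ) − e^(−72λ))/(36λ). This gives 0.879 for GTR and 0.735 for ATL.
- Deaths among 85 + 85: 85 × 0.879 + 85 × 0.735 ≈ 137.2.
- Schoenfeld power: Φ(√(137.2 × 0.25) × 0.481 − 1.96) = Φ(0.857) = 80.4%. A simulated log-rank test (10,000 runs) gives 80.2%.
- Inflation: 170/0.955 = 178.01. Expected non-glioblastoma patients: 178 × 0.045 = 8.01.

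The sample size is therefore sound, and about 8 replacements are expected.

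**2. How many patients are affected.** The number not confirmed among 178 follows Binomial(178, 0.045), with mean 8 and 2.5% and 97.5% quantiles of 3 and 14. The mITT population from 178 randomised therefore ranges from 178 − 14 = 164 to 178 − 3 = 175.

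**3. What within-arm replacement gains.** Power is Φ(√(d·a·(1−a)) × 0.481 − 1.96), where d is the number of deaths and a the ATL share.

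| ATL:GTR in mITT | Deaths | OS power |
|---|---|---|
| 80:90 | 137.9 | 80.5% |
| 85:85 | 137.2 | 80.4% |
| 90:80 | 136.5 | 80.1% |

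For every split of 8 exclusions out of 89:89 (from 0:8 to 8:0), power lies between 80.2% and 80.5%. Restoring exact balance gains essentially nothing.

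**4. Whether 178 is a maximum.** P(more than 8 not confirmed among 178) = 0.409, so 178 randomised patients give fewer than 170 confirmed in 41% of trials. At least 95% assurance of 170 would need 183. The cost of a shortfall is small: 82:82 = 164 patients give 132.3 deaths and 79.0% power.

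**5. Conditional worst case for bias.** This is an assumption, not something the article shows. Suppose that all 8 places are known in advance, 4 per arm, with ATL places filled by patients of prognostic HR h and GTR places by patients of 1/h.
- Shift in ln HR ≈ 2 × (4/85) × |ln h|; standard error = 2/√137.2 = 0.171.
- h = 0.5: shift 0.065, or 0.38 standard errors; two-sided error rises from 5% to 6.7%.
- h = 0.7: shift 0.034, or 0.20 standard errors; two-sided error 5.4%.
- With only half of the places steered, the errors are 5.4% and 5.1%.

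**The case against.** The strongest reply is that the sentence is loose wording. The article calls all 178 patients randomised, defines the mITT population as randomised patients, and describes a single allocation route. It mentions no reserved place, manual override or second list. How a replacement is issued is operational detail that a condensed article may leave to the full protocol.

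Part of this stands. A reader might infer that centres know in advance when an ATL or a GTR place is due. The article does not support that. Centre is not a stratification factor, and the trial is multicentre. Nothing says that a replacement goes to the centre that lost a patient, or that sites are told. Openness is justified by the impossibility of blinding surgery, which does not make upcoming allocations visible. Allocation is issued during surgery, after consent, so steering would need knowledge already at screening.

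A reader might also infer that the type I error is inflated. That holds only under the worst case in step 5, whose inputs have no support in the article. Stratification by age and KPS would limit steering on those two factors if replacements stay within stratum.

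The reply does not remove the contradiction. The missing mechanism may be a detail, but the article states a rule on the arm of the replacement, and that rule conflicts with the block list even if no site ever learns of it.

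**Conclusion.** The point holds as a contradiction that should be corrected. Taken literally, the replacement rule departs from the stated randomisation for about 8 patients. The number not confirmed among 178 has a 95% range of 3 to 14, assuming independent diagnoses at the plan's 4.5%. Predictability is a risk created by the rule, not a demonstrated fact, and no bias in the OS or QoL comparison has been shown.

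The rule has no offsetting benefit, since OS power changes by at most about 0.3 percentage points between 85:85 and the splits examined. The target of 170 and its 80% power are correct under exponential survival. The word maximum is wrong if 170 confirmed patients are required, but the practical loss is about 1.4 points of power (80.4% − 79.0%) at the lower end of the range.

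**What to change.** In the Sample size calculation section:

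1. Delete the within-arm replacement and keep the exclusion. Suggested text: *All 178 patients are allocated from the concealed stratified block list; no place is reserved or re-issued for an arm. Patients without glioblastoma IDH-wildtype are excluded from the mITT population only and remain in follow-up.*
2. In place of the maximum, write: *178 randomised, expected mITT 170 (95% range 164 to 175).*
3. Align the sentence on replaced patients in the section on drop-outs and missing data, so that it refers to exclusion and not replacement.

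The cost is a few sentences, and no special function is needed in the eCRF randomisation. The mITT population may end slightly away from 85:85 or a few patients below 170, with the small power losses shown above. If within-arm allocation was never intended, the same edit removes the contradiction.

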### Endpoints

The primary endpoint is OS in the modified intention-to-treat (mITT) population, defined as all randomized patients with histologically confirmed glioblastoma (CNS world health organization (WHO) grade 4, isocitrate dehydrogenase (IDH)-wildtype (wt)). If significant differences in OS are observed, the patient-reported QoL domain "global health status" from the European organization for research and treatment of cancer (EORTC) QLQ-C30 questionnaire will serve as a co-primary endpoint. Overall superiority of ATL requires a significant improvement in OS alongside non-inferiority in the development of global health status over time within the mITT population. Secondary endpoints include OS in the population of all patients randomized in the trial (intention-to-treat, ITT population) and in the per-protocol (PP) population. The QoL domain "global health status" from the EORTC QLQ-C30 questionnaire will also serve as a co-endpoint in these analyses, analogous to the primary endpoint. PFS, measured from the day of randomization until diagnosis of progressive disease based on MRI (RANO 2.0 criteria) [27], will be analyzed in the ITT, mITT, and PP populations. Separate OS and PFS analyses will also be conducted for patients with IDH-mutant gliomas. Further secondary endpoints will be evaluated in the mITT population and include QoL across six preferred domains of the EORTC QLQ-C30 and BN20 questionnaires (global health status, physical functioning, social functioning, cognitive functioning, communication deficit, and motor dysfunction), as well as all other domains of these questionnaires. Additional endpoints include PFS (as defined above), the KPS, the mRS, neurocognitive functioning assessed using the Verbaler Lern- und Merkfähigkeitstest (VLMT) [28, 29], the Boston Naming Test [30], and EpiTrack® [31], as well as seizure outcomes classified according to the International League Against Epilepsy (ILAE) [32].

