### Number of subjects

A total of 178 subjects will be randomized in a 1:1 ratio between the experimental and control arms.

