### Handling of drop-outs, withdrawal, and missing data

Subjects who drop out of the trial prior to randomization will be categorized as screening failures, with the reasons for drop-out documented in a comprehensive list.

Subjects who drop out of the trial after randomization will be analyzed using all available data, except for those replaced due to a disconfirming diagnosis of glioblastoma. These subjects will be excluded from the efficacy analysis.

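### Replacing patients without confirmed glioblastoma within their own arm conflicts with the stated block randomisation, and excluding them from efficacy contradicts the planned ITT and IDH-mutant analyses

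*Protocol article*

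**What the plan says.** **Replacement and allocation.** Under Sample size calculation, a patient whose final diagnosis does not confirm IDH-wildtype glioblastoma stays in safety follow-up, but such patients "will be replaced in their respective groups and excluded from the mITT population". The next sentence adds: "This replacement strategy will result in a maximum of 178 randomized patients". Number of subjects states: "A total of 178 subjects will be randomized in a 1:1 ratio between the experimental and control arms". Under Randomization, "Randomization will be performed using the method of permuted blocks with variable block sizes", and "The randomization number will be assigned through the electronic case report form (eCRF) system, in a 1:1 ratio", with strata formed by age group and pre-operative KPS. Assignment takes place during surgery, after the frozen section, and is open. No separate route for a replacement patient is described.

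**Analysis.** Under Handling of drop-outs, withdrawal, and missing data, subjects who leave after randomisation are analysed with all available data, "except for those replaced due to a disconfirming diagnosis of glioblastoma. These subjects will be excluded from the efficacy analysis". Under Endpoints, however, "Secondary endpoints include OS in the population of all patients randomized in the trial", and PFS is to be analysed in the ITT, mITT and PP populations. Definition of populations puts the IDH-mutant patients in the ITT population, uses that population for sensitivity analyses of survival and QoL, and plans a separate exploratory analysis of OS, PFS and QoL in the IDH-mutant patients. Primary outcome and Secondary outcome variables repeat these requirements.

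**The concern.** Replacing a patient within a group means that a later patient has to enter that group. A permuted-block list with variable block sizes gives the next patient in a stratum whatever assignment comes next, so it cannot promise a particular arm. If staff followed the replacement sentence literally, the arm of some later patients would be fixed before they were enrolled.

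That would matter in this trial for three reasons. Treatment is open. Final histology is recorded in the eCRF, and Table 1 schedules its collection at day 30. Several eligibility decisions made before randomisation rest on the treating neurosurgeon's judgement: whether complete resection is achievable, whether lesions beyond the margins belong to the tumour, and whether GTR would come close to ATL in extent. Replacement patients with confirmed glioblastoma would also enter the mITT set, on which the confirmatory OS test is run.

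The second issue does not depend on how replacement is read. An unrestricted exclusion from efficacy would remove exactly the patients who distinguish the ITT population from the mITT population. A reader of the results could no longer see whether dropping patients after randomisation affects the conclusion.

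**Working it through.** **1. The plan's own figures.** Inputs from Sample size calculation: 170 evaluable patients, 4.5% expected without glioblastoma, maximum 178 randomised.
- 170 / (1 − 0.045) = 178.01, which agrees with 178.
- 178 × 0.045 = 8.0 patients expected to trigger the rule.
- 178 × 0.955 = 170.0 expected to remain evaluable.

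The inflation to 178 therefore already covers the expected loss, without steering anyone into an arm.

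**2. The 170.** Inputs from the same section: medians of 17 and 27.5 months, two-sided 5%, 36 months of accrual and 36 months of follow-up. Assumptions added here: exponential survival, uniform accrual, no loss to follow-up.
- HR = 17 / 27.5 = 0.618; |ln HR| = 0.481.
- Event probability = 1 − [exp(−λF) − exp(−λ(A+F))] / (λA), with λ = ln 2 / median and A = F = 36. This gives 0.879 for control, 0.735 for ATL, mean 0.807.
- Schoenfeld's formula needs 136 events for 80% power; 136 / 0.807 = 169 patients, which matches 170. Freedman's formula needs 141 events and 175 patients.

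**3. Does the design need equal mITT arms?** Power = Φ(√[d·a(1−a)] × |ln HR| − 1.96), where d is the expected number of events and a the control fraction. The extreme case starts from 89 per arm and takes all 8 exclusions from one arm.

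| Control / ATL | Expected events d | Schoenfeld power | Simulated power (8000 runs) |
|---|---|---|---|
| 85 / 85 | 137.2 | 80.4% | 80.7% |
| 89 / 81 | 89 × 0.879 + 81 × 0.735 = 137.8 | 80.5% | 81.0% |
| 81 / 89 | 81 × 0.879 + 89 × 0.735 = 136.6 | 80.2% | 80.3% |

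Arm-specific replacement gains nothing measurable in power.

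**4. Does a cap of 178 guarantee 170 evaluable?** No. With X distributed as binomial(178, 0.045), P(X > 8) is about 41% and P(X > 12) about 6%. With 12 exclusions, 166 remain. At 83 per arm, d = 83 × (0.879 + 0.735) = 134.0, and power = Φ(√134.0 / 2 × 0.481 − 1.96) = Φ(0.82), about 79.5%. The shortfall is small, and it arises under the cap with or without arm-specific replacement.

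**5. The exclusion rule set against the analysis sections.** No arithmetic applies.
- Every patient without confirmed IDH-wildtype glioblastoma is to be replaced (Sample size calculation).
- Replaced patients are out of the efficacy analysis (Handling of drop-outs).
- IDH-mutant patients do not have IDH-wildtype glioblastoma, so they are among those replaced.
- It follows that ITT minus the replaced patients equals mITT, and that the IDH-mutant efficacy analysis has no patients.
- Endpoints, Definition of populations, Primary outcome and Secondary outcome variables all require analyses in one or both of those sets. The drop-out rule and these sections cannot all be followed.

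**The case against.** The strongest reply on allocation is that nothing in the article says a replacement patient is assigned without randomisation. The sentence after the replacement rule counts the resulting total as randomised, Number of subjects says all 178 are randomised 1:1, and the mITT population consists of randomised patients only. The phrase could simply mean that recruitment continues by randomisation to make up the loss. This stands as a limit on what may be claimed. It does not remove the conflict, because the words tie replacement to the arm and no section says how such a patient is drawn. The benign reading also has a difficulty if it implies a target per arm: once one arm is full, the remaining allocations are forced.

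A reader might go further and infer that sites could foresee the next allocation. The documents do not support this. It would require that the replacement falls to the same site and stratum, that it is the next patient there, and that the site is told. None of this is stated, and the trial is multicentre with two stratification factors, variable block sizes and assignment by the eCRF system. The stated openness concerns the inability to blind surgery and MRI, not disclosure of upcoming assignments.

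On the analysis rule, the singular wording in the drop-out section could be meant for the primary mITT analysis alone, and the ITT rule is explicit elsewhere. That is probably the intention, but the sentence carries no such limit.

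Finally, an article condenses a fuller protocol, which may settle the mechanics. The point made here is not that detail is absent, but that statements in this document are incompatible as worded.

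**Conclusion.** Two contradictions in the text hold.

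First, replacement within the arm cannot be carried out literally under the only allocation scheme described. About 8 of 178 patients are expected to trigger the rule, assuming the plan's 4.5%. That figure is the expected share without glioblastoma. A reader might take it as the number of patients allocated non-randomly, but the plan does not say so, and it would be that number only if the literal reading were put into practice. No stated sample size figure is wrong on this point.

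Second, the unrestricted exclusion contradicts the ITT analyses of OS, PFS and QoL and the separate IDH-mutant analysis. If every patient without glioblastoma counts as replaced, following it as written would make ITT identical to mITT and leave the IDH-mutant analysis empty. It would be too strong to say that this second issue threatens the primary result: the mITT test excludes these patients under either reading.

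The power figures rest on exponential survival, uniform accrual and no loss to follow-up.

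**What to change.** 1. In Sample size calculation, delete the reference to replacement within the respective groups. State that every patient, including those added to offset other diagnoses, is randomised from the ordinary stratified permuted-block list through the eCRF.
2. State that 178 randomised patients is the limit that prevails, even if slightly fewer or more than 170 prove evaluable. Without this, a target of 170 evaluable and a cap of 178 can conflict.
3. In Handling of drop-outs, limit the exclusion to the mITT and PP analyses, and state that these patients remain in all ITT efficacy analyses and, where IDH-mutant, in the separate IDH-mutant analysis.

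The cost is wording. The mITT arms may differ by a few patients, with power still about 80% in the most uneven split of 8 exclusions. The evaluable number may fall slightly below 170; at 166, power is about 79.5%. The allocation wording should be settled before it has to be applied, because an allocation already made cannot be corrected in the analysis.
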